Power calculations (see Appendix 1 for more details) and resource availability suggested the adoption of a sample of 25 households from the village areas of the 58 schools receiving the intervention and of 20 households in the village areas of the 58 control schools. Farmers will be oversampled in both areas in the following way: 10 out of the 25 households in the 58 intervention villages will be farmer households and 5 out of the 20 households in the 58 control villages will be farmer households. This distribution of the sample between farmers and non-farmer households and between project control groups allows the construction of comparable samples (see Table 3).

**Table 3 T3:** Summary of sample sizes

	**Communes**	**Schools**	**Households**	**Farmers**	**Children**^**1**^
Control	58	58	870	290	2,700
HGSF	29	29	435	290	1,500
HGSF+	29	29	435	290	1,500
TOTAL	58	116	1,740	870	5,700

Note: 1) the number of children in an estimate based on an average of 2 children per family in families with children and 1.5 children per family in farmer households.

Households were randomly selected in the catchment areas of the selected schools for the survey interviews.^6^ The definition of ‘household’ in Mali is not straightforward as many families share the same living compound and polygamous families are common. A recent study [27] found that adding descriptions to a “restricted” definition of household (a group of people who normally live in your household – adopted by the DHS) increases the number of adult male members reported during the interview. This, however, does have a very limited impact on household characteristics, such as per capita food consumption, assets and agricultural production. We recommend the use of the restricted definition adopted by the Rapid Household Survey 2006, which reflects the LSMS experience in collecting data in developing countries. According to this definition, a (restricted) household is a group of people who normally live and eat together. Members spending less than three months with the household within a year should be excluded. Families living in the same compound should be considered as different (restricted) households, though the consumption section of the questionnaire was carefully designed in order to take into account the common use of food resources. Polygamous households were treated as distinct households if wives live and cook in separate houses.

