In practice, the sampling of households was not conducted via a previous census as this was considered too costly in terms of time and resources. We opted for interviewing village chiefs and building a list of enlarged households in the villages covered by the sample school. The listing also included an approximation of the size of the enlarged households. In addition, a number of farmer households was oversampled in each village. Chiefs (and members of the CGSs) were asked to list which farmers they would contact if they were to purchase food within the village for the provision of school meals. This latter information was used to single out the surplus farmers in the area (up to 10 in the project villages and up to 5 in the control villages that will be interviewed).

Enlarged households were randomly selected (with inclusion probability proportional to size) from the list provided by the village chiefs, and listings of the restricted households within each selected enlarged households will then be developed through interviews with household heads. A restricted household with children aged 5 to 15 was then randomly selected within each selected enlarged non-farmer household, and we estimate that each household will have at least two children in this age group. A similar selection procedure was used for farmer households when these exceed the numbers of 10 and 5 in the project and control villages, respectively. In farmer households though, no age criteria were used and the household was identified around the main agricultural holding unit of the enlarged household. This consists of the family members involved in the main production unit (land and livestock) in the enlarged household.

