### Income

No previous studies have investigated the impact of home-grown school feeding on farmers’ incomes and indeed this type of programme is entirely new. In addition, it is difficult to find programmes with effects similar to those of school feeding programmes. The Purchase for Progress programme by the World Food Programme, which similarly to the Malian school feeding programme purchases food for local producers, has modelled an increase in income by $50 dollars as a reasonable target for small African farmers. With a per capita GDP of $700 this corresponds to 7.5% of the average Malian income, though the income of small farmers is likely to be less than half the national average income. In addition, farm income is about 50% of total household income and the impact of a $50 increase on farm income is therefore much larger. We adopt 15% and 30% as minimum detectable effects of the programme on agricultural incomes of small farmers.

We adopt a conservative estimate of 10 farmers surveyed in each village, and based on data on agricultural incomes of Ghanaian farmers, we estimated the intra-class correlation coefficient (ϱ = 0.25) and the variance explained by site variability (B = 0.40). Note that given the high value of the standard deviation of income, similar in size to average income, the standardised difference and the percentage difference are almost equivalent. The probability of detecting an increase by 15% in agricultural income is 35% and the probability of detecting an impact of 30% is 88%. A power of 80% will be able to detect an income increase by 26%.

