### Conclusions

The power analysis suggests that the study will be able to detect an increase in enrolment by 5%, a 0.2 difference in test scores and an increase in farmers’ incomes by 25% between the school feeding interventions and the control group. The study will be able to detect changes in enrolment by 6%, differences in tests scores by 0.3 and changes in income by 40% between the regular school feeding and the HGSF+ components of the intervention see (Table 7).

**Table 7 T7:** Summary table of values used in the power calculations

	**Enrolment**	**Test scores**	**Agricultural income**
Alpha	0.05	0.05	0.05
N (observations)	55	25	10
J (schools)	2	2	2
K (clusters)	58	58	58
Intra Cluster Correlation	-	0.15	0.25
Between sites variability	-	0.20	0.40

While the sample size is well suited to the analysis of programme impact on attendance rates and test scores, it is clearly insufficient for the analysis of income effects of the HGSF+ intervention. However, we hope to overcome this problem in two ways: by increasing statistical power through restricted randomisation and by focussing on intermediate outcomes rather than on household income, a variable that has large variance and high within cluster correlation. First, in order to increase statistical power we will adopt ‘restricted randomisation’ [25]. We will use the baseline data collected at the village and school levels to remove the randomisation outcomes that would result in an unbalanced comparison of project and control communes. The randomisation of the HGSF+ component of the project within the 58 communes will be performed only within the restricted sample of balanced randomisation outcomes. Second, we will analyse intermediate indicators of household income such as input use (labour and other farm inputs, such as land, seeds and fertiliser) and farm capital use like animal traction, tools and simple machinery.

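### Farm-income power against control is computed with 10 farmers in every village, but at most 5 are planned in control villages; the stated 26% and 25% detectable increases are not reached at 80% power

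*Protocol article*

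**What the plan says.** The Income part of Appendix 1 sets the farmer count for the comparison with control: "We adopt a conservative estimate of 10 farmers surveyed in each village". Table 7 repeats this as 10 observations, 2 schools per commune and 58 communes, with an alpha of 0.05. The same part gives 35% power for a 15% increase, says that "the probability of detecting an impact of 30% is 88" per cent, and puts the increase detectable at 80% power at 26%. The Conclusions of Appendix 1 give 25% for the same comparison.

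The sampling plan, under Random assignment and manipulation of treatments, has different counts. Each intervention village supplies 10 farmer households within its sample of 25. For the control arm the plan is half that: "5 out of the 20 households in the 58 control villages will be farmer households". Table 3 agrees, with 290 control farmers (58 × 5) and 290 + 290 = 580 in the two intervention groups (58 × 10). The description of the listing makes both numbers upper limits: "up to 10 in the project villages and up to 5 in the control villages that will be interviewed".

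**The concern.** The power calculation and the sampling plan describe different samples. The calculation implies 10 × 2 × 58 = 1,160 farmers; the plan has at most 580 + 290 = 870. A count that is the most one arm can supply, and double what the other can supply, is not a cautious choice.

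Smallholder farmer income is named among the primary outcomes in the abstract, and it has the lowest power of the three outcomes in Appendix 1. The detectable increase against control is the figure a reader would use to judge whether a null income result means anything. It should rest on the sample that will be interviewed.

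**Working it through.** **Inputs.** Intra-cluster correlation ρ = 0.25, between-site share B = 0.40, K = 58 communes with one intervention and one control village each (Appendix 1, Income and Table 7). Alpha is 0.05; sidedness is not stated, so two-sided is assumed. Appendix 1 treats percentage and standardised differences as almost equivalent, because the standard deviation of income is close to its mean.

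**Formula.** For pairs of villages within communes, with n_T and n_C farmers per village:

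Var = [s² + 2ρ(1 − B) + (1 − ρ)(1/n_T + 1/n_C)] / K

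Here s² is the variability of the effect between communes. The article gives no value, so it is 0 unless stated. Power comes from the noncentral F with 1 and 57 degrees of freedom.

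**Reproducing the stated figures (35%, 88%, 26%).** With 10 and 10 and s² = 0, the bracket is 0.30 + 0.75 × 0.20 = 0.45, so SE = √(0.45/58) = 0.0881. Power is 39% at 15% and 92% at 30%, and the detectable increase is 25.1%. The printed inputs therefore do not reproduce the stated power, although 25.1% is close to the 25% in the Conclusions.

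With s² = 0.06, the bracket is 0.51 and SE = 0.0938. Power is 34.9% and 88.2%, which matches. The detectable increase is 26.7%, close to the stated 26% but not equal to it.

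**Is such a term plausible?** The test-score calculation uses the same design with 25 children in both arms, ρ = 0.15 and B = 0.20. Stated: 24%, 68% and 95% power at 0.1, 0.2 and 0.3, and a detectable difference of 0.23. With s² = 0 the results are 27%, 77%, 98% and 0.208. With s² = 0.07 they are 23%, 68%, 95.5% and 0.230. Both outcomes point to an unprinted term of 0.06–0.07, but this is an inference from the outputs.

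**The planned sample, 10 against 5.** The farmer term becomes 0.75 × (1/10 + 1/5) = 0.225 instead of 0.15.

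| Farmers (project / control) | s² | SE | Power at 15% | at 25% | at 26% | at 30% | Detectable at 80% |
|---|---|---|---|---|---|---|---|
| 10 / 10 | 0 | 0.0881 | 39% | 80% | 83% | 92% | 25.1% |
| 10 / 5 | 0 | 0.0951 | 34% | 73% | 77% | 87% | 27.1% |
| 10 / 10 | 0.06 | 0.0938 | 35% | 75% | 78% | 88% | 26.7% |
| 10 / 5 | 0.06 | 0.1004 | 31% | 69% | 72% | 84% | 28.6% |

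A normal approximation instead of F gives 10 against 5 with s² = 0 slightly more: 35% at 15%, 88% at 30% and a detectable increase of 26.7%. Power at 26% is then 78%, still below 80%.

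**The case against.** A reader might infer that the stated 88% power is simply wrong for this design. The documents do not support that. On the printed parameters alone, 10 against 5 gives 87–88% power at 30% and 34–35% at 15%, essentially the stated figures; it is 10 against 10 that misses them. The fall to 84% needs a term that the article does not print. That term is back-fitted and is not the only fit: dividing the variance by 1 − ρB = 0.9 has the same effect at 10 against 10 as s² = 0.05, although that rescaling does not reproduce the test-score figures. This objection stands against any claim that the 88% is refuted. It does not rescue the 26% or the 25%, which miss 80% power on either reading.

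The loss is also small, because between-village variance dominates. Like for like, the detectable increase rises by about 2 points (25.1% to 27.1%, or 26.7% to 28.6%), and power at 30% stays above 80%. With s² = 0.06, even 10 against 10 reaches only 78% at 26%, so in that case part of the miss is not due to the farmer count.

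The article is open about weak income power. Other general equilibrium effects warns that the number of villages may be too small for significant project-control comparisons on farmer outcomes and adds simulation analyses. That is a fair general caveat, but it does not correct the specific figures in Appendix 1.

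Finally, Survey instruments places the farm-income module in the household questionnaire, so households outside the farmer oversample may also report farm income. That is possible, but the Income part and Table 7 count only 10 per village and do not invoke it.

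**Conclusion.** The contradiction in the farmer count is certain on the text, and calling 10 conservative is wrong. Its numerical effect is modest. With the planned 10 and 5, power at a 30% increase is about 87% on the printed inputs, or about 84% if an effect-variability term near 0.06 was used, so the 88% is roughly kept or about 4 points too high. The increase detectable at 80% power is about 27–29%, not 26% or 25%; power at those two values is 72–77% and 69–73%.

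These figures assume a two-sided alpha of 0.05, the printed ρ and B, and that both caps are met in full. Finding fewer farmers than the caps would lower power further; the article gives no expected shortfall.

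**What to change.** The authors should rerun the farm-income calculation against control with 10 farmers per project village and 5 per control village, and print every parameter used, including any effect-variability term and the sidedness of the test. Only they can confirm which settings were used.

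They should then restate the Income part of Appendix 1, Table 7 and the Conclusions from that run, with an expected detectable increase of about 27–29%, and make the Income part and the Conclusions give the same figure. The wording about a conservative estimate should become a maximum of 10 farmers in project villages and 5 in control villages.

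The cost is one recalculation and edited text. Sampling and fieldwork do not change.

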### Comparing school feeding to HGSF+ (cluster randomized trial)

To estimate MDES we assume that 58 clusters (schools) will be randomly assigned to regular school feeding or HGSF+. Using standard simulations we observe that

•A 5% difference will be detected with 60% probability, while differences of 10% and 15% will be detected with certainty. At 80% power the minimum detectable difference is 6%.

•A standardised difference of 0.1 would be detected in 15% of cases, a difference of 0.2 would be detected in 41% of cases and a difference of 0.3 would be detected in 79% of cases. With power set at 80% the minimum detectable difference is 0.32.

•The probability of detecting an increase by 15% in agricultural income is 17% and the probability of detecting an impact of 30% is 50%. A power of 80% will be able to detect an income increase by 40%.

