### Test scores

Few studies have investigated the impact of school feeding on learning outcomes. Drèze *et al*. [32] reviewed the experimental evidence on the impact of school feeding on standardised test scores and found an average standardised effect size of 0.31 for math achievement tests, while no effect was found on reading tests. We adopt a 0.3 difference as the expected effect of the intervention on math test scores. Based on the Scrochet report, the recommended intra-cluster correlation coefficient for math and reading tests is 0.15. We also assume that only about half of the children interviewed will be able to take the test and we set the number of children tested per village at 25. Simulations of power as a function of minimum standardised detectable effect show that a standardised difference of 0.1 would be detected in 24% of cases, a difference of 0.2 would be detected in 68% of cases and a difference of 0.3 would be detected in 95% of cases. With power set at 80%, the minimum detectable difference is 0.23.

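### Two power figures for HGSF+ versus regular feeding contradict the rest of their set: power at 0.3 SD is about 75%, not 79%, and the 80% income limit is about 43%, not 40%

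*Protocol article*

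**What the plan says.** The section of Appendix 1 on school feeding versus HGSF+ gives three sets of results, which it attributes to simulation.

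- **Test scores:** power of 15% at 0.1 SD and 41% at 0.2 SD, followed by "a difference of 0.3 would be detected in 79% of cases. With power set at 80% the minimum detectable difference is 0.32".
- **Income:** power of 17% for a 15% increase, then "the probability of detecting an impact of 30% is 50%. A power of 80% will be able to detect an income increase by 40" per cent.
- **Enrolment:** power of 60% for a 5% difference, with an 80% limit of 6%.

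The Conclusions of Appendix 1 then say that the study will be able to detect "differences in tests scores by 0.3 and changes in income by 40% between the regular school feeding and the HGSF+ components of the intervention". The same section calls the sample well suited to attendance and test scores, but clearly insufficient for income effects of HGSF+.

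**The concern.** Once the number of clusters and the significance level are fixed, a single power value at a single effect size determines the standard error. The standard error in turn determines the effect detectable with 80% power. The figures within each set must therefore agree, and two do not.

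For test scores the conflict shows without calculation. Stated power rises 38 points between 0.2 and 0.3 SD, yet the last single point, from 79% to 80%, is said to need a further 0.02 SD.

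This is the contrast that isolates the home-grown and social-accountability package, and farmer income and learning are among the primary outcomes named in the Abstract. A reader would take power at 0.3 SD as essentially 80%, and a 40% income change as detectable with 80% power. On the plan's own inputs, each has about 75%.

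**Working it through.** **Inputs**

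- Clusters: "we assume that 58 clusters (schools) will be randomly assigned to regular school feeding or HGSF"+. Table 3 shows 29 communes and 29 schools in each of the two arms (regular-feeding row: "HGSF 29 29 435 290 1,500").
- Significance level, Table 7: "Alpha 0.05 0.05 0.05". Sidedness is not stated; two-sided is assumed.
- Test scores: "the recommended intra-cluster correlation coefficient for math and reading tests is 0.15" and "we set the number of children tested per village at 25".
- Income: intra-cluster correlation 0.25 and 10 farmers per village (Income section and Table 7). The Income section treats the income SD as about equal to the mean, so a 30% increase is about 0.30 SD.

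**Formulas**

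SE = √[(4/J) × (ρ + (1 − ρ)/n)], with J = 58. Power comes from the noncentral t with 56 degrees of freedom and noncentrality δ/SE. Power of 80% needs δ/SE = 2.851 (2.802 under a normal approximation), so the 80% limit is 2.851 × SE.

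**Step 1: reproduce the plan's figures from its inputs**

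Test scores: ρ + (1 − ρ)/n = 0.15 + 0.85/25 = 0.184; SE = √(0.184 × 4/58) = 0.1126.

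Income: 0.25 + 0.75/10 = 0.325; SE = √(0.325 × 4/58) = 0.1497.

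| Quantity | Stated | t, 56 df | Normal |
|---|---|---|---|
| Test scores, power at 0.1 SD | 15% | 14.1% | 14.4% |
| Test scores, power at 0.2 SD | 41% | 41.5% | 42.7% |
| Test scores, power at 0.3 SD | **79%** | **74.5%** | **75.9%** |
| Test scores, 80% limit | 0.32 | 0.321 | 0.316 |
| Income, power at 15% | 17% | 16.6% | 17.0% |
| Income, power at 30% | 50% | 50.4% | 51.7% |
| Income, 80% limit | **40%** | **42.7%** | **41.9%** |
| Income, power at 40% | 80% (by implication) | 74.7% | 76.2% |

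Everything reproduces to within about two points except the entries in bold and the power implied by the 40% limit.

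**Step 2: check internal consistency without using ρ or n**

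Solve for the SE that gives each stated power, then multiply by 2.851.

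- 79% at 0.3 SD needs SE = 0.1066, so the limit is 2.851 × 0.1066 = 0.304. Rounding of 79% (78.5–79.5%) allows 0.302–0.306. In the other direction, a limit of 0.32 (0.315–0.325) implies 73–76% power at 0.3 SD.
- 50% at 30% needs SE = 0.1504, so the limit is 2.851 × 0.1504 = 0.429, or 42.9%. Rounding of 50% (49.5–50.5%) allows 42.6–43.2%. In the other direction, a limit of 40% (39.5–40.5%) implies 55–57% power at 30%.

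The ranges do not meet in either case. The normal approximation gives the same implied limits (0.304 and 42.9%), so this step does not depend on the choice of test.

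**Step 3: look for a setting that rescues a whole set**

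- One-sided testing: 83.8% at 0.3 SD with a limit of 0.284; 63.1% at a 30% increase with a limit of 37.7%.
- 55 children per cluster: 79% at 0.3 SD, but then 45% at 0.2 SD and a limit of 0.305.
- A cluster-level covariate explaining 20% of the between-cluster variance: income limit 39.3%, but then 57% power at 30%.

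None of these reproduces a complete set.

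**Step 4: enrolment**

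60% power at 5 points implies a limit of 6.3 points, which rounds to the stated 6. Table 7 gives no intra-cluster correlation for enrolment, so nothing more can be checked.

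**The case against.** - **Simulation or reading error.** The article gives no replicate count, test statistic or software, so some noise is possible. That may explain how the figures arose, but they still disagree. The test-score figures for the other contrast (school feeding versus control) pass the same check: 68% at 0.2 SD and 95% at 0.3 SD both imply the stated 0.23.
- **Coarse rounding of the income limit.** The gap is only 2 to 3 points, and the conversion from SD units to percentages is itself approximate. This is plausible but unproven, since the corresponding limit in the Income section is given to the unit, as 26%. The approximation also cannot reconcile 50% at 30% with 80% at 40%, because both are on the same scale.
- **The 0.3 in the Conclusions.** A reader might infer that it carries the 79% error forward. The documents do not support that. The same section shortens 0.23 to 0.2 and 26% to 25%, so 0.3 reads as a shortened 0.32. It is still worth restoring, because 0.3 SD has about 75% power.
- **Precision of the replacements.** The t-test and the normal approximation differ by about a point, so ranges are safer than single values. This objection stands.
- **Little depends on it.** The article already concedes that the sample is insufficient for HGSF+ income. That is correct, but the concession covers income only and does not make the 40% right.

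**Conclusion.** Two figures are wrong as written. Test-score power at 0.3 SD should be about 75% (74–76%), which agrees with the stated limit of 0.32. The 80% limit for income should be about 43% (42–43%), which agrees with the stated 17% and 50%; power at a 40% increase is about 75%.

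Both errors are on the favourable side, but they are modest: 3 to 5 points of power for test scores and 2 to 3 percentage points on the income limit.

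A reader might go further and conclude that every limit for this contrast is overstated, including enrolment, or that the sample size must be revisited. Neither follows. The limit of 0.32 SD is correct, the enrolment pair is consistent after rounding, and correcting the income limit only reinforces what the article already admits.

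The internal contradiction rests only on 58 clusters and two-sided testing at 0.05. Identifying 79% and 40% as the figures at fault also rests on the Table 7 inputs and equal allocation of 29 and 29.

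**What to change.** In the Appendix 1 section comparing school feeding with HGSF+, change 79% to about 75% and the 40% income limit to about 43%. If the simulation files are available, rerun them first and state the test used, so that each set comes from one calculation.

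In the Conclusions of Appendix 1, give the limits for HGSF+ versus regular feeding as 0.32 SD for test scores and about 43% for income. Leave the enrolment limit at 6%.

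The cost is a text correction. The figures become slightly less favourable, and the sample size, allocation and analysis stay as they are.
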